### Sample size calculation

The sample size for the Saan Suk cRCT was calculated based on the primary outcome, i.e., the knowledge score, scaled to 0–100. Parameters were derived from a cross-sectional survey conducted in Chanthaburi in November 2024 (n = 687), with a resulting mean knowledge score of 57.35 and standard deviation (SD) of 15.23. An intracluster correlation coefficient (ICC) of 0.028 was obtained by fitting a random-intercept linear mixed-effects model with village as the clustering variable. Assuming a two-sided significance level of α = 0.05 and 90% power, the trial is powered to detect differences in mean knowledge scores between the intervention and control arms at the post-intervention assessment. We parameterised the expected effect using Cohen's *d* of 0.40 [35], corresponding to approximately six points on the 0–100 knowledge scale, based on the estimated SD from the cross-sectional survey. This effect size is considered a small-to-moderate improvement in educational intervention research, and it is viewed as a meaningful and achievable change in population knowledge over a short period.

Sample size adjustments accounted for clustering, a 15% allowance for both individual- and cluster-level attrition, and a 5% inflation to account for potential contamination. Based on these assumptions and operational feasibility, the final design includes 24 clusters (villages), with 12 clusters per arm, with an average cluster size of 42 participants (i.e., 6 VHVs per village, visiting 7 households each), resulting in a total sample size of 1008 individuals (504 per arm) (Fig 1).

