### Statistical analyses

The statistical analysis will follow the intention-to-treat (ITT) principle. All eligible and consenting household members selected for outcome assessment will be analysed according to the randomised allocation of their village, regardless of intervention exposure, adherence, protocol deviations, or withdrawal from intervention activities. The village is the unit of randomisation, while outcomes are measured at the individual participant level. All analyses will therefore account for clustering at the village level. The allocation groups will remain masked to the statistician where feasible, until the primary analysis code and outputs are finalised. The primary comparison will be between villages allocated to the Saan Suk intervention and villages allocated to the current practice. All effect estimates will be presented with 95% confidence intervals. Statistical significance will be assessed using two-sided tests with an alpha level of 0.05.

A per-protocol analysis will be conducted as a sensitivity analysis. Here, we will include participants in intervention villages who received at least three or four planned visits, and participants in control villages with no documented exposure to Saan Suk-specific materials or training content.

Baseline characteristics will be summarised by cRCT arm to assess the comparability of the randomised groups and to describe the study population. Because randomisation is conducted at the village level, baseline balance will be assessed at both the cluster and individual levels. Cluster-level baseline characteristics include sub-district, distance to neighbouring study villages, number of registered VHVs, and relevant ecological characteristics, i.e., land use classes (e.g., vegetation, agricultural areas) and land-use interfaces where contact between people and wildlife may occur. Individual-level baseline characteristics will include age, sex, education, income, occupation category, household size, prior experience of zoonotic infectious diseases, and prior awareness of zoonotic diseases. The baseline assessment of the outcomes will not be conducted due to restricted operational feasibility. The background characteristics will be presented as means and standard deviations or medians and interquartile ranges for continuous variables, and as counts and percentages for categorical variables. Cluster size variation will be described and considered in sensitivity analyses.

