The primary outcome is the total knowledge score at post-intervention assessment, treated as a continuous variable. Between-arm differences will be estimated using a linear mixed-effects model with identity link, consistent with the assumptions used for the sample size calculation. The model will include a fixed effect for trial arm (intervention vs control) and random intercepts for cluster (village) to account for within-cluster correlation. Pre-specified adjustment covariates include district, VHV ID, age group, sex, education category, and occupational category. Additional adjustment for further baseline variables will be considered if important imbalances are observed despite randomisation.

In addition to the total score, planned stratified analyses of domain-specific knowledge scores will be conducted using the same mixed-effects modelling framework. These analyses are considered exploratory and will not replace inference based on the total knowledge score. The intraclass correlation coefficient will be estimated for the primary outcome.

Secondary outcomes (behaviour, attitudes, self-efficacy, and contacts with zoonotic hosts) will be analysed using mixed-effects regression models appropriate to the scale and distribution of each outcome (e.g., linear mixed models for approximately continuous outcomes; ordinal or generalised linear mixed models for ordinal or non-normal outcomes). For all secondary analyses, cluster will be included as a random effect, and district and VHV will be included as fixed effects where relevant. Effect estimates will be reported with 95% CIs and two-sided p-values. All secondary analyses are exploratory and will be interpreted descriptively. No adjustment for multiple comparisons will be applied.

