We acknowledge that the implementation of the Saan Suk programme depends on the availability, motivation, and capacity of VHVs. VHVs are trusted community actors well placed to deliver household-level health education interventions; however, they may differ in experience, communication style, time availability, and confidence in delivering One Health content. To support intervention fidelity, VHVs in the intervention arm will receive standardised training during a two- to three-day workshop, including a manual, structured materials, and communication training. Adherence and fidelity will be monitored through visit documentation, conducted by VHVs and evaluated by the trial coordination team.

Village Heads will also play an important role in supporting trial implementation, including encouraging adherence to training and field procedures. Their involvement in the allocation process, including the public envelope draw, is intended to strengthen transparency, community acceptance, and local ownership. Village Head permission is necessary for the respective village participation in the study; however, individual informed consent will also be obtained from trial participants, including VHVs and adult household members, where they participate in study-specific procedures or outcome assessment.

Outcome assessment is based on self-reported information, including knowledge, attitudes, self-efficacy, behaviours, and contacts with local animal hosts. These outcomes are appropriate for evaluating behavioural determinants of zoonotic spillover prevention, but they are subject to self-report and social desirability bias, particularly after delivery of an educational intervention [44]. To reduce measurement bias, outcome assessors will be trained, standardised questionnaires will be used, and outcome assessment teams will remain blinded to the intervention allocation. The questionnaire was expert-reviewed, back-translated, and piloted in the target communities to improve clarity, cultural appropriateness, and acceptability. The questionnaire also includes items to collect information on potential baseline factors that may differ between the trial arms and, if necessary, can be adjusted for in the analysis. Non-self-reported outcomes of zoonotic disease prevention behaviour or spillover risk are not feasible within the scope of this trial.

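### The plan lets covariates chosen for observed imbalance join the primary model without saying whether that model replaces the pre-specified one or is a sensitivity analysis

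*Protocol article*

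**What the plan says.** The primary-outcome paragraph of Statistical analyses sets out a linear mixed model with a fixed arm effect and a random village intercept. It calls six adjustment covariates pre-specified: district, VHV ID, age group, sex, education category and occupational category. The same paragraph then states: "Additional adjustment for further baseline variables will be considered if important imbalances are observed despite randomisation". It gives no criterion for an important imbalance, no list of the further variables, and no status for the extended model.

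Earlier in that section, balance is to be described at two levels. At village level: "Cluster-level baseline characteristics include sub-district, distance to neighbouring study villages, number of registered VHVs, and relevant ecological characteristics". At individual level the list goes beyond the six covariates to income, household size, prior experience of zoonotic disease and prior awareness of it. The Discussion repeats the option, saying that the outcome questionnaire holds "items to collect information on potential baseline factors that may differ between the trial arms and, if necessary, can be adjusted for in the analysis".

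Other analyses are ranked. Per-protocol and imputed-data analyses are called sensitivity analyses, and domain scores are said not to displace the total score. Only the imbalance-driven adjustment has no rank.

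**The concern.** The primary test yields one p-value judged at two-sided 0.05. If covariates can be added after the arms have been compared, and the standing of the larger model is open, more than one model could be put forward as primary. With few clusters the trigger is easily met by chance. Observed imbalance is also a weak reason to select a covariate: what counts is how well it predicts knowledge, which the 2024 survey could indicate beforehand.

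Three things are at stake. The error rate could rise if the choice were made with results in view. Village-level degrees of freedom could be spent on variables that do not predict the outcome. And an open list could admit a variable that the programme itself has altered.

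**Working it through.** **Inputs (Sample size calculation).** "Assuming a two-sided significance level of α = 0.05 and 90% power"; "mean knowledge score of 57.35 and standard deviation (SD) of 15.23"; d = 0.40, "corresponding to approximately six points on the 0–100 knowledge scale"; "An intracluster correlation coefficient (ICC) of 0.028 was obtained"; 12 villages of 42 per arm.

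**The plan's own figure.**
- d × SD = 0.40 × 15.23 = 6.09 points.
- Individually randomised n per arm: 132 (d = 0.40) or 136 (6 points).
- Design effect: 1 + (42 − 1) × 0.028 = 2.148, giving 284 or 293 per arm.
- The plan then makes "a 15% allowance for both individual- and cluster-level attrition, and a 5% inflation to account for potential contamination". Taking 15% at each of the two levels, with 6 points, gives about 426 per arm. 426/42 = 10.1, so 11 villages; one extra small-sample village makes 12 per arm, or 24 × 42 = 1,008.

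The double 15% and the extra village are assumptions, since the text also cites operational feasibility. The sample size is not in dispute here.

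**Precision at 12 × 42 per arm.**
- Variance of a village mean: 15.23² × (0.028 + 0.972/42) = 11.86, SD 3.44.
- SE of the arm difference: √(2 × 11.86/12) = 1.41 points.
- Smallest significant difference: 2.07 (t, 22 df) × 1.41 = 2.9 points.
- The planned 6 points is 6/1.41 ≈ 4.3 SE; power is about 98%.

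**How often the trigger is met by chance.** The standardised difference on a village-level variable has chance SD √(2/12) = 0.41. The chance of exceeding an assumed 0.5 is that of exceeding 0.5/0.408 = 1.22 in absolute value: 22% (normal) or 23% (t, 22 df). For at least one of k independent candidates it is 1 − (1 − p)^k. That gives 63–66% for k = 4 and 78–80% for k = 6; simulation gave 66% and 81%.

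**Error and power, by simulation.** Two set-ups were used. Both have SD 15.23, ICC 0.028, 24 villages of 42, allocation balanced within district, and a base model of arm plus district. Set-up A works on village means with 4 or 6 village-level candidates and a 0.5 cut-off (6,000 trials per scenario). Set-up B fits the mixed model with four village-level and four individual-level candidates of nil, moderate or strong prognostic value, and cut-offs of 0.10, 0.20 and 0.25 (800 null trials per scenario, Monte Carlo SE about 0.8 percentage points).

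| Result | A | B |
|---|---|---|
| No effect, base model: p < 0.05 | about 5% | 3.8–4.5% |
| No effect, one cut-off applied mechanically | 3.4–5.3% | 2.3–5.3% |
| No effect, most favourable permitted model | 7.0–8.2% | 6.9–7.5% |
| True 3 points, power: base model | 52–54% | 54–56% |
| True 3 points, power: mechanical adjustment | 44–51% | 49–52% |

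The permitted models are all subsets of the imbalanced covariates in A. In B they are no addition, or any one of the three cut-offs.

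At a true 3 points, the permitted models in A disagree on significance in 11–24% of trials. In B, when the base-model p lies between 0.02 and 0.10, they disagree in about 41% of runs. A rerun of A at 6 points gave disagreement in only 2–5% of trials.

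**When the candidates are measured.** Table 2 lists as collected before the intervention: age, gender, household size, income category and number of ineligible household members. Prior awareness and prior experience are not on that list, although Statistical analyses counts them as baseline characteristics. The Discussion places adjustment items in the outcome questionnaire, which is given in the week after delivery ends. If prior awareness is recorded then, a programme meant to raise awareness could have changed the answer.

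**VHV ID.** There are 6 VHVs in each of 24 villages, 144 in all, and each belongs to one village and so to one arm. The indicators of the VHVs in intervention villages sum to the arm indicator. With VHV ID as a fixed effect, the arm effect cannot be estimated.

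**The case against.** The strongest reply has four parts.

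First, the core model is pre-specified, and the sentence says only that extra adjustment will be considered. A reader might infer that the deciding model is not fixed at all, or that an extended model will be reported as primary. The text says neither: what is open is the optional addition and its status.

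Second, the imbalance criterion and variable list are commonly left to the statistical analysis plan, which the Discussion mentions and which is not shown. So their absence is not the point. The point is that the protocol itself grants a data-driven addition inside the primary-model paragraph and leaves it unranked.

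Third, imbalance can be judged without outcome data, and mechanical adjustment does not inflate the error. The 7–8% arises only if someone selects among models by result, which the protocol does not describe. It also counts significance in both directions: in the rerun of A, a search ending in significance favouring the intervention occurred in 3.8–4.5% of null trials, against a nominal 2.5%. Masking the statistician hides the direction, although a two-sided p-value can still be read from masked labels. All of this stands and limits the size of the concern.

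Fourth, the planned effect is far from the significance limit, so the choice would rarely change the conclusion there. That also stands.

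**Conclusion.** The point holds as a cheap improvement, not as a flaw that undermines the trial. The plan permits imbalance-driven covariates in the primary model without ranking the result, and with 24 villages the occasion will probably arise (about 63–81%). Mechanical use holds the error at about 2–5% with some loss of power. Selection with results in view could bring the two-sided error to about 7–8%. The practical effect is on results near 3 points, seldom at 6.

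A reader might infer that the trial's error rate is 7–8%, or worse. A free search over all 256 subsets of eight candidates gave 10–29% in set-up B, but that includes variables that are not imbalanced, which the sentence does not allow. Nothing in the documents indicates that models would be chosen by result.

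The figures rest on assumed cut-offs, numbers of candidates, independence between them and prognostic strengths, none of which the protocol gives; land-use variables in particular may be correlated. The simulated base model held arm and district only, not all six listed covariates. The bias from adjusting for prior awareness is conditional on its being measured after the intervention.

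**What to change.** In the primary-outcome paragraph of Statistical analyses:

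- State that the primary conclusion rests only on the arm effect from the mixed model with the covariate set fixed in advance.
- State that models adding variables because of observed imbalance are sensitivity analyses and do not replace that result.
- Restrict those variables to ones measured before the intervention or that it cannot alter.
- Name now any village-level variable thought to predict knowledge, for example from the 2024 survey, and include it whatever the observed balance.
- When closing the list, do not enter VHV ID as a fixed effect. Use a random effect for VHV within village, or omit it.

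Align the matching sentence in the Discussion.

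The cost is a few sentences. Sample size and data collection do not change, and no participants had been enrolled at submission. The downside is that a chance imbalance on an unlisted prognostic variable would be addressed only in a sensitivity analysis.

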### Ethical considerations

This study has been approved by the Ethics Commission of the Medical Faculty of Heidelberg University (reference number: S-607/2025 on the 14^th^ April 2026) and is registered in the DRKS registry (Registration ID: DRKS00038582; date of registration: 11^th^ May 2026). Before enrollment, all participants are informed about the study’s objectives and their right to withdraw at any time without any negative consequences, and provide written informed consent.

Any protocol modifications or amendments will be submitted to the relevant ethics committees for approval before implementation. Approved amendments will be communicated to the trial registry, investigators, and study staff. All deviations from the protocol during trial implementation will be documented in a protocol deviation log, reviewed by the trial coordination team, and considered in the analysis where relevant.

### The status and timeline of the study

The trial is expected to start on 27 of July 2026 and continue until October 2026. Below, we present the participant timetable (Table 2). Recruitment of villages, VHVs, and households is planned to start on 27 July 2026 and be completed on 16 August 2026. The intervention implementation will start on 17 August 2026 and last for four weeks. Outcome assessment will be conducted between 14 and 30 September 2026 in both trial arms. Database lock is planned for November 2026. No participants have been enrolled at the time of submission. A manuscript reporting the main trial results is expected to be submitted for peer review in the third quarter of 2027, when the trial results will become available.

**Table 2 pone.0354989.t002:** Schedule of enrollment, interventions, and assessments for the Saan Suk Trial.

TIMEPOINT	TRIAL PERIOD (in Weeks)											
		Enrollment			Post-Randomisation							
	−1–0	1	2	3	4	5	6	7	8	9	10	11
**ENROLLMENT:**												
Eligibility check, selection of villages and VHVs	x											
Scoping visits and stakeholder engagement	x											
Enrollment of villages, Informed consent (Village Heads)		x										
Enrollment of VHVs by VHV Head and Village Heads, Information sheet and consent		x										
Enrollment of households by VHVs, Verbal informed consent			x	x								
**RANDOMISATION:**												
1:1 random allocation of villages to intervention and control		x										
**INTERVENTION IMPLEMENTATION:**												
*Intervention arm*												
Training of the trainers			x									
Trainers train VHVs				x								
VHVs conduct community meetings				x	x							
VHVs conduct household visits for intervention sessions						x	x	x	x			
*Control arm*												
VHV conducts household visits as standard practice					x	x	x	x	x			
**ASSESSMENT**												
Baseline variables* of household members				x								
Post-intervention outcome assessment in household members in the intervention arm										x	x	
Post-intervention outcome assessment in household members in the control arm										x	x	

*Variables are collected to compare arms and randomisation balance: age, gender, number of people in household, household income category, and number of ineligible people in household. The baseline does not include a full outcome assessment due to study feasibility constraints.

## Discussion

In this cluster randomised controlled trial, we will evaluate the effects of a co-designed One Health educational intervention delivered through Thailand’s existing Village Health Volunteer system in rural communities in Chanthaburi Province. The co-design approach is intended to ensure that the intervention is desirable, acceptable, and feasible within the target communities of Thailand. By leveraging existing VHV training and community health structures supported by the Ministry of Public Health, the Saan Suk programme has the potential to be integrated into the routine VHV activities if it is shown to be effective and feasible.

The choice of cluster randomisation is grounded in the nature of the intervention and its intended mode of delivery. If scaled up, the Saan Suk intervention would be implemented at the village level through registered VHVs, rather than delivered to isolated individuals. Village-level randomisation, therefore, reflects the expected implementation pathway and supports community acceptance and feasibility of the randomisation procedures. It also reduces the risk of contamination between participants within the same community. Nevertheless, intervention spillover (contamination) between trial arms remains possible because of participant mobility and close communication with family members, friends, and neighbouring communities. To reduce this risk, villages must be located at least 2 km apart to be eligible for inclusion in this trial, and community engagement meetings will emphasise the importance of not sharing study-specific procedures, materials, or content with neighbouring villages during the study period. The distance for the restriction was chosen to be feasible for selecting the required number of villages and based on expert opinion on residents’ travel frequency. Potential contamination will also be assessed through selected questions in the outcome assessment questionnaire.

We acknowledge that the implementation of the Saan Suk programme depends on the availability, motivation, and capacity of VHVs. VHVs are trusted community actors well placed to deliver household-level health education interventions; however, they may differ in experience, communication style, time availability, and confidence in delivering One Health content. To support intervention fidelity, VHVs in the intervention arm will receive standardised training during a two- to three-day workshop, including a manual, structured materials, and communication training. Adherence and fidelity will be monitored through visit documentation, conducted by VHVs and evaluated by the trial coordination team.

Village Heads will also play an important role in supporting trial implementation, including encouraging adherence to training and field procedures. Their involvement in the allocation process, including the public envelope draw, is intended to strengthen transparency, community acceptance, and local ownership. Village Head permission is necessary for the respective village participation in the study; however, individual informed consent will also be obtained from trial participants, including VHVs and adult household members, where they participate in study-specific procedures or outcome assessment.

Outcome assessment is based on self-reported information, including knowledge, attitudes, self-efficacy, behaviours, and contacts with local animal hosts. These outcomes are appropriate for evaluating behavioural determinants of zoonotic spillover prevention, but they are subject to self-report and social desirability bias, particularly after delivery of an educational intervention [44]. To reduce measurement bias, outcome assessors will be trained, standardised questionnaires will be used, and outcome assessment teams will remain blinded to the intervention allocation. The questionnaire was expert-reviewed, back-translated, and piloted in the target communities to improve clarity, cultural appropriateness, and acceptability. The questionnaire also includes items to collect information on potential baseline factors that may differ between the trial arms and, if necessary, can be adjusted for in the analysis. Non-self-reported outcomes of zoonotic disease prevention behaviour or spillover risk are not feasible within the scope of this trial.

Participant retention and complete follow-up may be affected by livelihood patterns, agricultural work, seasonal mobility, weather, and competing community activities. Activity logs will be conducted regularly by the trial coordination team. Field teams will document reasons for non-response, discontinuation, or missing data, and the analysis will account for clustering and missingness in accordance with the pre-specified statistical analysis plan.

Finally, the trial will be conducted in a specific ecological, cultural, and health-system context. The findings will be most directly applicable to rural Thai communities where VHVs are active and where community members regularly interact with wildlife, domestic animals, and shared environments. However, the intervention development process, delivery model, and evaluation framework may be relevant to other settings aiming to strengthen community-based pandemic prevention and One Health literacy through existing community health structures. Results will be disseminated through peer-reviewed open-access publications and presentations at scientific conferences, irrespective of study outcome. Findings will also be shared with local and national stakeholders in Thailand, including community feedback sessions where appropriate. A summary of results will be made available to study participants and communities in an accessible format (e.g., via the project website). Trial results will be reported in the relevant trial registry to the responsible ethics committees, in accordance with applicable reporting requirements.

Overall, the Saan Suk trial addresses an important evidence gap regarding whether a co-designed, theory-informed, VHV-delivered One Health intervention can improve community knowledge, behavioural determinants, and self-reported practices related to zoonotic disease prevention, thereby contributing to the broader pandemic prevention agenda.

